The most frequently encountered pathological entity in TBI patients is an acute intracranial hematoma. Specifically, an acute subdural hematoma (ASDH) is the most common injury in elderly TBI patients and is often accompanied by a cerebral contusion [8, 9]. The enlarged subdural space of the progressively atrophic aging brain is associated with increased tension on bridging veins, making them more susceptible to shearing damage. Furthermore, the widespread use of anticoagulants and antiplatelet drugs among elderly increases the risk for ASDH development, even after low to moderate energetic head trauma [10]. Traditionally, older age has been closely associated to poor outcome after TBI [11, 12], partly because of comorbid illnesses negatively influencing outcome [12]. In reports from the 1980s and 1990s, mortality rates for patients aged ≥65 with an ASDH approached 90% [13, 14]. Hence, elderly patients have long been treated less “aggressively” compared to the younger patient population because of the presumed poor prognosis [10]. Over time, with faster transfers directly from accident to level I trauma hospitals, improved diagnostic tools and acute medical and intensive care, mortality rates in elderly patients with ASDH have declined from 90 to between 30 and 60% [15]. Along with this, neurologists’, trauma- and neurosurgeons’ traditional reserved attitude towards elderly patients has gradually shifted towards a more “aggressive” surgical approach [16, 17]. Despite this trend towards a more intensive treatment approach in the elderly sustaining TBI, the question whether to surgically or conservatively manage elderly patients with an ASDH remains a matter of huge controversy [18]. Surgical evacuation of the hematoma can be lifesaving, but is not necessarily restorative and may leave patients in a questionable quality of life, with huge costs to family and society [19–22]. Conversely, non-operative management may prompt favorable outcome in some patients, but can also result in—potentially preventable—death and disability [23, 24]. At present, it is not possible to accurately predict whether a specific patient will benefit from a certain treatment in terms of survival, functional recovery, and quality of life. This heterogeneity can be caused by many factors, including gender, anticoagulant/antiplatelet use, premorbid functioning, comorbidities, age, and the presence or absence of intracerebral contusions accompanying the ASDH. Current Brain Trauma Foundation (BTF) guidelines for the surgical management of TBI recommend the surgical removal of an ASDH measuring > 10 mm or when it causes a midline shift > 5 mm, regardless of a patient’s neurological state (Glasgow Coma Scale (GCS) score) [25]. These guidelines, released in 2006, are based on low-grade (class C) evidence from the 1990s and thus provide only limited guidance in modern clinical practice, allowing for subjective care and practice variation [23–26]. Indeed, great variation in BTF guideline adherence has been reported, ranging from 18 to 100% between studies [27, 28]. Moreover, major practice variation exists in Belgium and The Netherlands with regard to the management of traumatic ASDHs between centers, and even between neurosurgeons in the same center [29–31]. This variability in TBI management goes alongside unexplained variability in outcome and large between-center differences unrelated to case-mix [32–34].

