### Sample size {14}

The sample size of 300 patients was based on an ordinal analysis method of the primary outcome. It was calculated analytically using PASS software version 11 and achieves a 90% power to detect a change in the log odds ratio of 0.69 with a 0.05 (two-sided) significance level, allowing for a loss of follow-up of 8%. Calculations were based on the expected percentage distribution of conservatively treated patients over the GOS-E categories 1–8 (15, 10, 10, 10, 10, 10, 15, 20) with category 1 and 2 combined and an estimated (adjusted) proportional odds ratio of 2.0 representing the targeted treatment effect that is considered clinically relevant in the management of elderly with a traumatic ASDH. Table 4 shows the corresponding distribution of patients over the GOS-E outcome categories. The rationale for combining GOS-E categories 1 and 2 in the statistical analysis is the opinion of the researchers that a potentially large shift of patients from category 1 (death) to category 2 (vegetative state) should not result in a positive trial as this cannot be considered a beneficial or positive effect of surgery.

**Table 4 Tab4:** Estimated shift over GOS-E outcome categories

GOS-E	1&2	3	4	5	6	7	8
Patient’s condition	Dead and vegetative state	Lower severe disability	Upper severe disability	Lower moderate disability	Upper moderate disability	Lower good recovery	Upper good recovery
Initial conservative treatment (%)	25	10	10	10	10	15	20
Early surgery (%)	14	7	8	9	10	19	33

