#### Secondary study parameters

For all secondary study parameters, subjects in both arms of the study will be compared using the appropriate tests, based on the ITT population. Graphic data displays may also be used to summarize the data. Statistical analyses may include logistic and linear regression models, Fisher’s exact tests, or chi-square tests and Student’s *t* tests or Mann-Whitney *U* tests (depending on normality of data). The interaction of different operative techniques with treatment arm outcome will be addressed in our subgroup analysis by a Cox Proportional Hazard model with the “day of discharge from the rehabilitation center, nursing, or hospital facility to the own home” as an endpoint/event, which is considered a relevant endpoint from both a QOL and a health-economic perspective. Importantly, analyses of subgroups representing dichotomized continuous variables may also be performed by an interaction-effect analysis.

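### The exploratory Cox model for discharge home has no rule for death, and the imputation rule makes no exception for visits after death

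*Protocol article*

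**What the plan says.** All references are to the protocol article.

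- **Statistical methods {20a}, Secondary study parameters.** The general rule is "For all secondary study parameters, subjects in both arms of the study will be compared using the appropriate tests, based on the ITT population". A list of tests that may be used follows. The interaction of operative technique with treatment arm is assigned to a Cox model in the subgroup analysis, with the event "day of discharge from the rehabilitation center, nursing, or hospital facility to the own home". The text calls this endpoint relevant to quality of life and to health economics. It does not say what happens to a patient who dies before going home.
- **Outcomes {12}, Other study parameters.** Subgroup analyses, including craniotomy versus added decompression, are described as exploratory.
- **Sections {18b} and {20c}.** Missing follow-up values are imputed from the same patient's other follow-up data. Patients who die early stay in the analysis because death is a category of the primary GOS-E. No rule for death is given for the other scales, and the imputation sentence does not separate a visit missed from a visit after death.
- **Frequency of death.** Sample size {14} plans on 15% deaths under conservative treatment. The background section reports that "mortality rates in elderly patients with ASDH have declined from 90 to between 30 and 60" per cent.

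**The concern.** Discharge home cannot happen after death. A standard Cox fit treats a death as censoring, so the patient leaves the risk set and the model describes the rate of going home among those still alive and not yet home. That quantity can be reported as such, but it is not the chance of getting home, which is what a reader of this endpoint will take from it. If two groups differ in mortality, the two quantities separate. The technique comparison may well involve such groups: the background section itself refers to high morbidity and mortality after decompressive craniectomy.

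The imputation rule raises a different problem. A patient seen at 3 months who dies before 6 months has other follow-up data. Read literally, the rule produces a 6-month and a 12-month QOLIBRI, EQ-5D-5L or MOCA score for that patient. For EQ-5D-5L, such values would also feed the QALY.

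**Working it through.** **1. The plan's own figure.** Inputs from Sample size {14}: "achieves a 90% power to detect a change in the log odds ratio of 0.69"; two-sided 0.05; "an estimated (adjusted) proportional odds ratio of 2.0 representing the targeted treatment effect"; "allowing for a loss of follow-up of 8" per cent. Whitehead's proportional-odds formula with the Table 4 distributions (mean proportions 0.195, 0.085, 0.09, 0.095, 0.10, 0.17, 0.265; sum of cubes 0.0341):

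n per arm = 6 × (1.960 + 1.282)² / [0.69² × (1 − 0.0341)] = 137.1, so 138 per arm and 276 in total; 276 / 0.92 = 300.

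The stated N is reproduced. Nothing below changes it. The article gives no figure for the time-to-home analysis.

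**2. Deaths implied by the plan.** Conservative arm: 15% dead (the further 10% are vegetative). With a common odds ratio of 2.0, the surgical odds of death are (0.15/0.85)/2 = 0.0882, giving 0.0882/1.0882 = 8.1%. Per 150 patients that is about 22 versus 12 deaths. Table 4's 25% versus 14% combines death and vegetative state. Vegetative patients are alive and stay at risk, so those figures cannot serve as death rates here.

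**3. Mechanism.** Suppose 55% go home in both groups (assumption). Among patients who do not die, that is 55/85 = 64.7% against 55/91.9 = 59.8%. The group with fewer deaths has a larger risk set and so a lower rate of going home per patient at risk, although the same share gets home.

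**4. Size.** Simulation with 40,000 per group, follow-up to day 365 and exponential event times. Assumptions not in the documents: the share going home; median 7 or 30 days to death; median 30 or 60 days to home; the additional survivors do not go home within the year. The hazard ratio is for the group with fewer deaths; ranges run over the four timing combinations.

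| Deaths | Home, each group | HR, deaths censored | HR, deaths kept at risk |
|---|---|---|---|
| 15% vs 8.1% (planning values) | 55% | 0.90 to 0.94 | 1.00 to 1.01 |
| 30% vs 15% (assumed contrast) | 55% | 0.74 to 0.83 | 1.00 to 1.01 |
| 60% vs 30% (assumed contrast) | 35% | 0.43 to 0.69 | 1.00 to 1.01 |

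The standard error of the log hazard ratio is about 0.01, so about 0.89 to 0.94 is a fair summary of the first row. The 30% and 60% levels come from the background section; halving them in the other group is an assumption.

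**5. Quality of life among survivors.** Suppose other survivors score 60 and the additional survivors score 30 (both assumed). At 15% versus 8.1% deaths the survivors' mean in the lower-mortality arm is (0.85 × 60 + 0.0689 × 30)/0.9189 = 57.75, a difference of −2.25. Scoring death as 0 gives 0.0689 × 30 = +2.07. The sign depends on the rule for death. Under the plan's own uniform shift, however, the survivors' mean GOS-E is 6.16 with surgery and 5.47 without, and no reversal occurs.

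**The case against.** The strongest case is that most of this belongs in a statistical analysis plan that is not shown. The list of tests is permissive, the Cox model is exploratory, and time to discharge home is not in the list of secondary outcomes. A cause-specific hazard ratio is also a legitimate quantity if reported as such, and the article does not say that deaths are censored.

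Much of this stands and limits the point. A reader might infer that the secondary analyses ignore death altogether. They do not: secondary GOS-E is stated to include mortality, and the QALY can count death. A reader might also infer that QOLIBRI, EQ-5D-5L, MOCA and length of stay will be tested in survivors only. The tests are left open, the imputation rule could lead to the opposite fault, and length of stay is observed in patients who die in hospital. For length of stay the issue is only interpretation: early death shortens the stay. Nor can it be said that a life-saving arm will look worse. That needs the additional survivors to do poorly, which is not what the planning model assumes. Finally, the simulation is a two-group contrast, not the planned technique-by-arm interaction, so it shows direction and order of size only.

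Two things do not fall to the objection. The article names both the model and the event, and death rules out that event. It also states an imputation rule that, as written, covers visits after death.

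**Conclusion.** The point holds in a limited form. The Cox model for discharge home needs a stated treatment of death. With deaths censored, and at the protocol's planning death rates, the hazard ratio would be about 0.89 to 0.94 against the group with fewer deaths when equal shares go home. This rests on the assumed 55% going home, the assumed event times, and additional survivors not going home within a year; the distortion is larger at higher mortality. The imputation rule needs an exception for death; this follows from the text and needs no arithmetic. The documents do not support a claim that all secondary analyses are biased, or that surgery will be made to look worse. The matter deserves correction because it is cheap to correct. It does not threaten the trial's main conclusion.

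**What to change.** 1. **Discharge home:** report cumulative incidence of discharge home and of death by group, with death as a competing event. Give a Fine-Gray model alongside the cause-specific hazard ratio, and say which question each answers.
2. **Imputation ({18b} and {20c}):** state that values are not imputed for visits after death.
3. **EQ-5D-5L:** set utility to 0 from the date of death.
4. **QOLIBRI and MOCA:** label results among survivors as descriptive, or add a sensitivity analysis that ranks death worst.
5. **Length of stay:** keep the outcome, and read it alongside in-hospital mortality.

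The cost is wording, some programming and a few sentences of explanation in the report. No new data collection is implied, and the primary analysis and N = 300 stay as they are.

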#### Possible return of investment (ROI)

The financial consequences of TBI for individuals and society are substantial in both Belgium and The Netherlands. TBI is associated with significant direct healthcare costs in terms of pre-hospital care, emergency care, hospitalization, long-term post-discharge care, and rehabilitation, as well as indirect costs, i.e., due to loss of productivity of both patient and family [5]. The total direct and indirect costs of TBI in Europe were estimated to €33 billion [58]. In 2012, estimated annual costs of TBI in the Netherlands were €314.7 million, with €158.8 million direct and €155.9 million indirect costs [5]. The mean total costs per TBI case were €18,030 [5]. Since then, these costs have probably increased. Recent work from the investigators shows that mean in-hospital costs were €24,980 per ASDH patient and primarily the result of costs related to admission (€14,980) and surgical intervention (€6,890) [59]. In this regard, a large amount of costs could be saved if early surgery turns out not to be more effective than a conservative treatment strategy. On the other hand, if surgery turns out to be more effective, an incremental cost-utility analysis could prove surgical treatment to be the most cost-effective strategy. In line with this, a study has shown that aggressive surgical management of severe TBI in patients aged 60–80, despite being the most expensive treatment strategy, was also the most cost-effective strategy on the long term because it resulted in better outcome and thus lower costs associated with long-term nursing care and lost productivity [60, 61]. In fact, this is probably an underestimation of the true effect because current methods of cost analysis are not sensitive enough to capture the contributions (for example, familial childcare or retirement spending habits) of the older population to society. Similarly, the loss of productivity of caregiving family members is probably overlooked in most analyses. The investigators propose to assess the cost-effectiveness of treatment by performing a cost-effectiveness analysis (CEA) and a cost-utility analysis (CUA). The results of these health-economic analyses will lead to more cost-effective treatment of this rapidly increasing patient group in an economically challenged healthcare system. They will give insight in the magnitude of the problem and quantify the cost-effectiveness of complex trauma care in the fragile elderly, which have been excluded in previous studies. This study holds great potential for return of investment, especially since the implementation percentage is expected to be high because high-quality evidence is lacking and clearly awaited. In any case, the results of this trial will better inform societal health-economic discussions and improve health-economic moral deliberations.

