#### Cost-effectiveness and cost-utility analysis

An incremental cost-effectiveness ratio (ICER) will be calculated comparing the costs and effects between the surgical and conservative treatment group. A CUA will be performed for which the QALY, calculated based on the EQ-5D-5L summary score, is the outcome measure. For the CEA, the primary effect measure will be the GOS-E. The costs and effects will be discounted. A 1-way, 2-way, and probabilistic sensitivity analysis will be performed to determine the effect of uncertainty in all input parameters.

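### The only stated criterion for choosing a t test or a Mann-Whitney test is normality, which points skewed costs to a rank test although the trial's cost question is about means

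*Protocol article*

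**What the plan says.** The protocol article lists costs, direct and indirect, among the secondary outcomes, both under Objectives {7} and under Outcomes {12}. In Statistical methods {20a}, Secondary study parameters, it states: "For all secondary study parameters, subjects in both arms of the study will be compared using the appropriate tests, based on the ITT population". The next sentences are permissive: "Statistical analyses may include logistic and linear regression models", followed by Fisher's exact or chi-square tests and then "Student’s *t* tests or Mann-Whitney *U* tests (depending on normality of data". Costs are not excepted. The same section sets p < 0.05 as the threshold for significance.

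Costs also have their own economic evaluation under {20b}. It takes healthcare and societal perspectives over 1 and 5 years and follows national guidelines. In Cost-effectiveness and cost-utility analysis it states: "An incremental cost-effectiveness ratio (ICER) will be calculated comparing the costs and effects between the surgical and conservative treatment group". Discounting and one-way, two-way and probabilistic sensitivity analyses are added. No test or interval is named there for the cost difference itself.

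The background section on return of investment frames costs as means: "mean in-hospital costs were €24,980 per ASDH patient", of which €6,890 is attributed to surgery.

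**The concern.** A decision about budgets or savings needs the mean cost per patient, because mean times number of patients gives the total. The ICER's numerator is likewise a difference in mean costs. Mann-Whitney asks a different question: whether a randomly chosen patient in one arm tends to cost more than a randomly chosen patient in the other. The two questions agree when the distributions have the same shape and can part company when they do not.

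Different shapes are plausible here. Group A patients are assigned surgery, so nearly all of them carry its cost. Group B patients are operated on only after deterioration, so their extra cost tends to sit in a minority. A rank test gives that expensive tail little weight. With equal mean costs it can therefore report surgery as dearer, beside an ICER whose cost difference is near zero. Patient-level costs are usually right-skewed, so a normality criterion would choose the rank test for the very outcome it suits least.

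**Working it through.** **The plan's own figure.** None is stated for the cost comparison. The number analysed follows from Sample size {14} and the 1:1 allocation: 300 × (1 − 0.08) / 2 = 138 per arm.

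**Inputs from the documents.** Mean in-hospital cost €24,980; surgical component €6,890; significance level 0.05.

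**Assumed, because the documents give no cost SD or distribution.** Lognormal non-surgical costs with a stated coefficient of variation (CV); a share d of group B operated on late; and a ratio r of non-surgical cost in those patients to that in other group B patients.

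**Step 1. In-hospital costs with equal true means.**

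- Group A: €6,890 + lognormal with mean 24,980 − 6,890 = €18,090.
- Group B: lognormal with mean *b* for a share 1 − d, and €6,890 + lognormal with mean r × *b* for a share d.
- Equal means require *b* = (24,980 − d × 6,890) / [(1 − d) + d × r]. For d = 0.3 and r = 3, *b* = (24,980 − 2,067) / (0.7 + 0.9) = 22,913 / 1.6 = €14,321.

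Share of simulated trials with p < 0.05:

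| d | r | CV | Mann-Whitney | Welch |
|---|---|---|---|---|
| 0.2 | 2 | 1.0 | 62.5% | 4.9% |
| 0.3 | 3 | 0.7 | 89.7% | 5.9% |
| 0.4 | 1.5 | 0.7 | 25.0% | 5.5% |
| 0.2 | 1 | 0.7 | 19.1% | 5.1% |
| 0.4 | 1 | 0.5 | 8.8% | 5.8% |

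Repeat runs put the Mann-Whitney range at about 8-90%. Nearly all rejections had the higher median in group A. Shapiro-Wilk rejected normality of group B's costs in more than 99% of runs, so a normality criterion would select Mann-Whitney for such data.

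**Step 2. A different model as a cross-check.** Both arms lognormal with mean €24,980 and unequal CVs. The median is mean / √(1 + CV²). For CV 0.6 in A and 1.0 in B:

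- medians: 24,980 / √1.36 = €21,420 and 24,980 / √2 = €17,664;
- log-scale variances: ln 1.36 = 0.307 and ln 2 = 0.693;
- P(A > B) = Φ[(0.693 − 0.307) / 2 / √(0.307 + 0.693)] = Φ(0.193) = 0.576, although the means are equal.

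Mann-Whitney rejects in 58.5% of these trials and Welch in 5.7%. With CV 0.8 and 1.0 it rejects in 17.6%. With CV 1.0 in both arms, which is the same shape, it rejects in 5.1%, so the test holds its level there.

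**Step 3. Adding costs after discharge.** The trial's outcome is wider than in-hospital cost. The five scenarios of Step 1 were rerun with an assumed lognormal post-discharge cost (CV 1.5), the same in both arms and independent of in-hospital cost. With €25,000-50,000 added, Mann-Whitney rejects in about 5-19% and Welch stays at about 5%. The most extreme scenario falls from about 90% to about 19% with €25,000 and to 8-9% with €50,000.

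**The case against.** Four counter-arguments carry weight.

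- **The text does not assign a test to costs.** It speaks of appropriate tests and of analyses that may be included, and linear regression, which compares means, comes first in the list. This stands. A reader might infer that the plan sends costs to Mann-Whitney. It permits that and points that way, but does not require it.
- **Costs have their own economic plan.** The ICER and the probabilistic sensitivity analysis work with costs and effects and not with ranks. This stands too. A reader might infer that the cost-effectiveness conclusion rests on a rank test, and it does not. However, the economic sections neither withdraw costs from the secondary-outcome comparison nor name a test or interval for the cost difference, so a separate cost p-value remains possible.
- **The large percentages concern in-hospital cost only.** The planned outcome includes long-term care, rehabilitation, travel and lost productivity. This stands, as Step 3 shows. In addition, €6,890 is the surgical part of a mean per ASDH patient, not a stated cost per operated patient. The Discussion also expects lower in-hospital costs with less early surgery, so equal in-hospital means are a condition for testing the method, not a forecast.
- **A protocol article may leave the choice of test to the analysis plan.** That would answer a complaint that no test is named. Here a selection criterion is named, and it is the wrong one for costs.

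**Conclusion.** The point holds in limited form. For a listed secondary outcome whose meaning lies in the mean, the only stated criterion for choosing between Student's t and Mann-Whitney is normality, which favours the test that does not address the mean. The consequence is a cost p-value that may disagree with the mean cost difference behind the ICER. The primary endpoint, the sample size and the ICER are unaffected.

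The size cannot be fixed from the documents. With equal means and 138 per arm, Mann-Whitney rejects in about 8-90% of trials on in-hospital cost alone, in about 5-19% once an assumed common post-discharge cost of €25,000-50,000 (CV 1.5) is added, and in 5% when the arms' distributions have the same shape. Welch's test stays at about 5%. These ranges rest on assumed CVs, late-surgery shares and cost ratios. Post-discharge costs that differ between arms could move them either way. A reader should not take the upper in-hospital figures as the error rate for the trial's full cost outcome.

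**What to change.** In Secondary study parameters (or the analysis plan), exempt costs from the normality criterion with a sentence such as: costs are compared between arms as the difference in arithmetic means with a 95% confidence interval, by non-parametric bootstrap or Welch's t test, whatever their distribution. This makes the secondary cost comparison consistent with the ICER.

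QALYs are not a listed secondary outcome, so they belong in Cost-effectiveness and cost-utility analysis. Costs and QALYs can be bootstrapped jointly there, so that the same resamples describe the uncertainty around the ICER.

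The cost is one sentence, a little more analysis work and possibly a wider interval. No new data are needed.
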